#### Acceptability

A 5-item acceptability measure was created based on the topic guide for the semistructured interviews. The topic guide itself was informed by the theoretical framework of acceptability [22]. Using a 5-point Likert scale, participants in the intervention were asked to rate their satisfaction with the intervention (affective attitude), perceived effectiveness of the intervention, their confidence in performing the behaviors required to participate (self-efficacy), the perceived amount of effort required to participate (burden), and the extent to which they understand how the intervention is intended to work (coherence).

### Statistical Analysis

To maximize power and conform to intention-to-treat analysis, missing data will be handled using multiple imputation methods (ie, the expectation-maximization algorithm) if assumptions regarding mechanisms of missingness are met.

A series of 3 (baseline, T1, and T2) × 2 (control and intervention) mixed ANOVAs will be performed to determine the efficacy of a lifestyle information and education session and goal setting mHealth intervention on clinical, psychological, and health behavior measures.

Independent sample *t*-tests will be used to analyze group differences (control and intervention) in average daily step count across the 24 weeks of the study.

Thematic analysis of interview transcripts will be used to explore the acceptability of the Moving On program for recipients.

Quantitative data will be analyzed with IBM SPSS Statistics 24. NVivo 12 will be used to facilitate organization and analysis of qualitative data.

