#### Sample Size

The statistical program G*Power was used to conduct power analysis. With 2 groups (intervention and control), 3 measurements (baseline, time 1, and time 2), an assumed correlation among repeated measures of 0.3, and a small-medium effect size and a power of 0.8, the recommended sample size for repeated measures analysis of variance (ANOVA) was 102. Sample size calculations were made considering attrition rates (approximately 20%) observed in similar studies using mobile technology interventions with cancer survivors [24].

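### The missing-data rule defines multiple imputation as the expectation-maximization algorithm, a different method; followed as a single fill, it would inflate type I error or dilute the treatment effect

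*Protocol article*

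**What the plan says.** The Statistical Analysis section of the protocol article gives the purpose of imputation as "To maximize power and conform to intention-to-treat analysis", and then the rule: "missing data will be handled using multiple imputation methods (ie, the expectation-maximization algorithm) if assumptions regarding mechanisms of missingness are met". The next paragraph gives the analysis that will use the filled data: "A series of 3 (baseline, T1, and T2) × 2 (control and intervention) mixed ANOVAs will be performed". The software is also fixed: "Quantitative data will be analyzed with IBM SPSS Statistics 24".

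The section does not mention random draws, a number of imputations, pooling, or whether treatment arm is in the imputation model. The Sample Size section plans for attrition of about 20% and uses "an assumed correlation among repeated measures of 0.3".

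**The concern.** The parenthesis opens with the abbreviation for 'that is', so EM is offered as the definition of the multiple imputation and not as one ingredient of it. The two are different procedures. EM is a maximum-likelihood algorithm for a mean vector and covariance matrix. Multiple imputation draws each missing value at random several times, analyses each completed dataset, and pools so that the uncertainty about the missing values enters the standard error.

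A 3 × 2 mixed ANOVA needs a complete row for every participant and treats every entry as observed. If its input is one dataset filled with EM conditional means, one of two things goes wrong:

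- **Arm in the EM model:** the filled values lie exactly on the fitted arm-specific regression. The effect is unbiased, but the error variance is too small.
- **Arm not in the EM model:** the filled values are pulled towards a regression common to both arms, and the arm difference shrinks.

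The rule covers every clinical, psychological and health behavior outcome analysed by these ANOVAs. A second, smaller fault is that imputation is conditional on missingness assumptions being met. Missing at random cannot be verified from the observed data, so the condition cannot be applied as a check.

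**Working it through.** **Inputs from the protocol article.** 61 control and 62 intervention participants; three visits; correlation 0.3; planned attrition about 20%. From the Procedure section, 55 of 62 and 53 of 61 attended the first session, so 7 + 8 = 15 of 123 (12.2%) did not.

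**Assumptions, not in the article.** Two-sided alpha 0.05; normal data with equal correlations; completely random monotone dropout, with missingness at 12 weeks (T1) set to 0.7 times that at 24 weeks (T2); correlation 0.8 as a sensitivity value; a true effect of 0 or 0.40 SD at T1 and T2. 1,500 simulated trials per setting.

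**1. The plan's own figure.** The article states that "the recommended sample size for repeated measures analysis of variance (ANOVA) was 102", for "a small-medium effect size and a power of 0.8". The effect size is not given as a number; f = 0.15 is assumed. For the group-by-time interaction, λ = f²·N·m/(1 − ρ) = 0.0225 × 102 × 3 / 0.7 = 9.84, with 2 and 2 × (102 − 2) = 200 degrees of freedom. Power is 0.802, so 102 is reproduced.

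**2. Check on the simulation.** With no missing data, the standard error (SE) of the arm difference in change from baseline to T2 is √[2(1 − ρ)(1/61 + 1/62)]. This is √(1.4 × 0.03252) = 0.213 at ρ = 0.3 and √(0.4 × 0.03252) = 0.114 at ρ = 0.8. The simulation gives the same values.

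**3. Why a single fill understates error.** Rubin's rules give total variance T = W + (1 + 1/M)·B, where W is the within-imputation variance, B the between-imputation variance and M the number of imputations. A single conditional-mean fill has no B. Its W is also too small, because the filled values carry no residual noise.

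**4. Change to T2 at 20% missing (14% at T1).** Reported and true SE and type I error are from the runs with no effect; the estimate is from the runs with a true effect of 0.40 SD.

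| Method | ρ | Reported SE / true SE | Estimate of 0.40 SD | Type I error, t-test |
|---|---|---|---|---|
| EM, arm in model | 0.3 | 0.199 / 0.227 = 0.88 | 0.398 | 9.2% |
| EM, arm in model | 0.8 | 0.104 / 0.125 = 0.83 | 0.401 | 9.2% |
| EM, arm left out | 0.3 | 0.199 / 0.197 = 1.01 | 0.324 | 4.5% |
| EM, arm left out | 0.8 | 0.104 / 0.104 = 1.00 | 0.332 | 5.0% |
| Proper multiple imputation, M = 20, arm in model | 0.3 | 0.232 / 0.228 = 1.02 | 0.399 | 4.5% |
| Proper multiple imputation, M = 20, arm in model | 0.8 | 0.127 / 0.125 = 1.02 | 0.401 | 4.4% |

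At ρ = 0.3 the single fill reports an SE of 0.199, which is below the 0.213 that complete data on all 123 would give. With a true effect of 0.40 SD, the fill with arm rejects in 51.3% of trials, against 39.7% under proper multiple imputation. That apparent gain in power comes from the understated SE.

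**5. The planned test, the 3 × 2 group-by-time interaction, with arm in the EM model.** Type I error is 12.4 to 12.7% at 20% missing. At 13% missing it is 8.2% (ρ = 0.8). Separately coded simulations gave 8.3 to 9.0% and about 9 to 10% at roughly 8% missing at T1 and 12% at T2, and 10.9 to 12.4% at 15% and 20%. The range over 12 to 20% missing is therefore about 8 to 13%.

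**6. Dilution with arm left out.** At 13% missing, 0.357 SD is estimated in place of 0.40: 1 − 0.357/0.40 = 11%. At 20% missing, 1 − 0.324/0.40 = 19% and 1 − 0.332/0.40 = 17%. Type I error stays near 5%.

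**The case against.** The strongest reply is that the article never says one EM-filled dataset will be analysed. It says multiple imputation. EM only estimates parameters, and how values are then filled, and how many times, is a separate step that the article does not describe. If the analysts draw and pool properly, the numerical harm disappears. This stands, and it makes the sizes above conditional. It does not rescue the sentence, which names a procedure and equates it with a different one. That is not a detail left for an analysis plan to supply: a plan that follows the article would use EM, and a plan that specifies real multiple imputation would contradict it.

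It is also fair that the two harms exclude each other, and that which one applies depends on the variables in the imputation model, a detail an article may omit. So neither the direction nor the exact size of the error can be read from the article.

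Some stronger readings are tempting but not supported:

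- **Larger inflation.** With 30% missing at T2, type I error reaches 15.8% at ρ = 0.3 and 19.0% at ρ = 0.8, but 30% has no source in the article.
- **Invented participants.** All 123 attended baseline. At 14% and 20% missing, the filled share of the T0 to T2 values is (0 + 14 + 20)/3 = 11%.
- **Reversion to listwise deletion, so that intention-to-treat lapses.** The article names no fallback and does not say that missing at random will be tested.

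**Conclusion.** The rule is wrong as written: EM is not multiple imputation, and the article defines one as the other. If it is carried out as a single EM fill feeding the 3 × 2 ANOVAs, the group-by-time test has a type I error of about 8 to 13% instead of 5% with arm in the EM model. With arm left out, the effect is diluted by about 11 to 19% in the runs shown.

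These sizes rest on 12 to 20% missing at T2, correlations of 0.3 to 0.8, normal data and completely random dropout. The 20% is the article's planning figure. The 12.2% is non-attendance at the first session, used here only as a guide, because missingness at T1 and T2 is not reported. A reader might infer that the trial's P values are in fact inflated; the article does not establish that. If pooled multiple imputation was intended, the correction is one of wording only.

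**What to change.** Delete the parenthesis that names EM and state one of two methods:

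- **Proper multiple imputation:** random draws, treatment arm in the imputation model, a stated number of imputations (for example 20), and pooling by Rubin's rules.
- **A likelihood-based mixed model** using all observed data from the 123 randomised participants, without imputation.

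Replace the condition that missingness assumptions be met with a statement that the analysis assumes missing at random, since the observed data cannot verify it. Nothing wider is needed to cure this defect.

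Both methods are available in SPSS 24 and neither needs new data. The cost is a little more analysis work, and wider standard errors than a single EM fill with arm included would report. The Results section says analysis was already underway, so the method actually used should be stated explicitly when results are reported.

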**Methods:**

A sample of 123 cancer survivors (body mass index >25 kg/m^2^) was randomly assigned to the control (n=61) or intervention (n=62) group. The intervention group attended a 4-hour tailored lifestyle information session with a physiotherapist, dietician, and clinical psychologist to support self-management of health behavior. Over the following 12 weeks, participants engaged in personalized goal setting to incrementally increase physical activity (with feedback and review of goals through short message service text messaging contact). Objective measures of health behavior (ie, physical activity) were collected using Fitbit (Fitbit, Inc). Data on anthropometric, physiological, dietary behavior, and psychological measures were collected at baseline (T0), 12 weeks (T1; intervention end), and 24 weeks (T2; follow-up). Semistructured interviews were conducted to explore the retrospective acceptability of the Moving On program from the perspective of the recipients.

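### The plan defines multiple imputation as the expectation-maximization algorithm; if the ANOVAs are run on a single data set filled in that way, the arm-by-time test is anti-conservative or the effect is diluted

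*Protocol article*

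**What the plan says.** All of the analysis wording is in the Statistical Analysis section of the protocol article.

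- **Missing data.** To preserve power and intention-to-treat, "missing data will be handled using multiple imputation methods (ie, the expectation-maximization algorithm". This applies "if assumptions regarding mechanisms of missingness are met".
- **Main analysis.** "A series of 3 (baseline, T1, and T2) × 2 (control and intervention) mixed ANOVAs will be performed" for the clinical, psychological and health behavior measures.
- **Step counts.** These are handled apart: independent-sample t-tests "will be used to analyze group differences (control and intervention) in average daily step count across the 24 weeks of the study".

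The Sample Size section supplies the only planning figures for missingness and correlation: "attrition rates (approximately 20%) observed in similar studies" and "an assumed correlation among repeated measures of 0.3, and a small-medium effect size and a power of 0.8". The sample of 123 "was randomly assigned to the control (n=61) or intervention (n=62) group".

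**The concern.** The sentence names one procedure and then defines it as another. EM is a way of obtaining maximum likelihood estimates. When it is used to fill in data, each gap receives its predicted value once. A conventional ANOVA on the result has no means of knowing which values were observed.

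Two things can then go wrong, depending on a choice that the article does not state:

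- **Arm in the EM model.** The filled values sit exactly on each arm's prediction. The residual variance is too small, the sample size is counted as if complete, and the test rejects too often.
- **Arm not in the EM model.** Missing values in both arms are pulled toward a common prediction, so the estimated difference shrinks.

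The condition on the missingness mechanism gives no protection, because both problems arise even when data are missing completely at random. At stake are the ANOVA-based efficacy tests on incomplete outcomes. The step meant to support intention-to-treat would distort those tests.

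**Working it through.** **Inputs from the article.** N = 123 (61 control, 62 intervention); three visits; correlation 0.3; power 0.8; attrition about 20%. **Assumed, because not stated:** two-sided alpha 0.05, normal outcomes, compound symmetry, data missing completely at random, no auxiliary variables. Missingness at T1 and T2 is not in the text available, so it is varied.

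**1. The plan's own figure.** For the within-between interaction, λ = f²·N·m/(1 − ρ). With f = 0.15, N = 102, m = 3 and ρ = 0.3, λ = 0.0225 × 102 × 3 / 0.7 = 9.84. On 2 and 200 degrees of freedom the power is 0.802. The stated 102 is therefore reproduced if small-medium means f = 0.15 and the target is the arm-by-time interaction. The checks below focus on that test.

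**2. Rough check, arm modelled.** Take one follow-up visit with fraction m missing and no correlation to borrow from.
- The true variance of an arm mean is σ²/[n(1 − m)].
- The ANOVA on filled data estimates about σ²(1 − m)/n.
- The ratio is 1/(1 − m)², so the actual type I error is 2[1 − Φ(1.96(1 − m))].
- At m = 0.20 this is 2[1 − Φ(1.568)] = 11.7%. At m = 0.12 it is 2[1 − Φ(1.725)] = 8.5%.

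This is a single contrast at zero correlation, so it checks plausibility only.

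**3. Rough check, arm omitted.**
- If all dropout precedes T1, the missing values are predicted from baseline alone, which carries no treatment effect. The effect shrinks by about m, here 20%, at both visits.
- If half drop before T1 and half before T2, the T1 effect shrinks by 10%. At T2, the 10% who still have a T1 value recover about ρ/(1 + ρ) = 0.3/1.3 = 0.23 of the effect. The remaining effect is about 0.80 + 0.10 × 0.23 = 0.823, a loss of about 18%.

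**4. Simulation of the 3 × 2 mixed ANOVA** (61/62 participants, ρ = 0.3, 20% dropout; 3,000 null runs per pattern, 1,500 runs with a true 0.5 SD effect at T1 and T2).

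| False-positive rate | Staggered dropout | All dropout before T1 |
|---|---|---|
| Complete data, interaction | 4.2% | 4.7% |
| Single EM, arm modelled, interaction | 9.2% | 12.6% |
| Single EM, arm modelled, group main effect | 6.2% | 8.2% |
| Single EM, arm omitted, interaction | 4.7% | 4.9% |
| Multiple imputation, 20 draws, arm modelled, pooled | 4.7% | 5.4% |

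| Effect estimate, SD | Complete data (T1, T2) | EM, arm modelled (T1, T2) | EM, arm omitted (T1, T2) | Loss, arm omitted |
|---|---|---|---|---|
| Staggered | 0.509, 0.497 | 0.508, 0.497 | 0.457, 0.411 | 10%, 17% |
| All before T1 | 0.489, 0.495 | 0.491, 0.496 | 0.391, 0.395 | 20%, 20% |

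The loss is 1 minus the ratio to complete data, for example 1 − 0.411/0.497 = 17%. Across repeated runs at these planning values, the ranges are about 9–13% for the false-positive rate and about 10–21% for the shrinkage.

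**5. Sensitivity.** Correlation was varied over 0.3–0.9.
- At 12–13% dropout, the false-positive rate with arm modelled is about 7–11%, and the shrinkage with arm omitted is about 5–16%.
- At 20% dropout, the false-positive rate with arm modelled is about 9–16%.
- At 30% dropout, the two figures are about 14–23% and 13–32%.
- A Greenhouse-Geisser correction does not help: at correlation 0.7 and 20% staggered dropout, the rate is 12.3% without it and 12.0% with it.

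Monte Carlo error on the false-positive rates is about 0.5–1 percentage point.

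**The case against.** The strongest reply is that multiple imputation is the governing phrase and EM only a parenthesis, so the authors may intend real multiple imputation and have described it badly. In that case the wording is wrong but the analysis need not be. The number of imputations, the pooling and the variables in the imputation model are details that an article commonly leaves to the analysis plan. This stands: the article does not settle which procedure will be run, so every figure above is conditional on single EM fill-in. It does not remove the point, because the text positively identifies the method as EM; it does not merely leave detail out.

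A reader might infer that every ANOVA in the trial will have a false-positive rate near 10–12%, or an effect cut by a sixth. The documents do not support that, for four reasons.

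- **Missingness is unknown.** The article gives a planning rate of about 20%. It also reports that 55 of 62 and 53 of 61 attended their first session, so 15 of 123 (12%) did not. The baseline table covers 53 + 54 = 107 people, so the text does not establish that all 123 records will be filled in.
- **Outcomes and tests differ.** Outcomes with little missing data are barely affected, the group main effect is inflated less than the interaction, and step counts are compared by t-test.
- **The two branches are not equally damaging to p values.** With arm omitted, type I error holds near 5%. The harm is dilution of the effect and some lost power, not false positives.
- **The power loss from omitting arm can be overstated.** With 0.5 SD at T1 and T2 and 12%/20% missing, interaction power was about 66% with complete data, 63% for an ideal likelihood analysis of the observed data, and 58% for EM without arm. Only about 5 points are attributable to the method.

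**Conclusion.** The point holds in conditional form. Equating multiple imputation with EM is an error in the text as written, whatever a later document adds. If the mixed ANOVAs are run on one EM-completed data set as if it were observed, then at 20% attrition and correlation 0.3 the arm-by-time test rejects a true null in roughly 9–13% of trials when arm is in the EM model. The effect estimate is then essentially unbiased. When arm is left out, the test keeps its level but the effect is understated by roughly 10–21%, more at T2 than at T1 if dropout is staggered.

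These figures rest on alpha 0.05, data missing completely at random, normal outcomes and compound symmetry, and they move with the amount and timing of dropout and with the correlation. The stronger conclusion, that the trial's efficacy tests are all invalid, does not follow: neither the procedure actually run nor the missingness at T1 and T2 is known from the text.

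**What to change.** Delete the parenthesis that names EM, and state one of the following:

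1. A likelihood-based linear mixed model for repeated measures on all observed values, with arm, visit and arm-by-visit. It needs no filled-in data.
2. Genuine multiple imputation: arm in the imputation model, random draws, a stated number of data sets, and results pooled by Rubin's rules. In the check above, 20 draws with arm simply included as a variable brought the false-positive rate back to about 5%.

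Add that the ANOVAs will not be run on an EM-completed data set.

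The cost is a sentence of wording and slightly more analysis work, with no new data. The article says analysis is underway, so if EM fill-in has already been used, the affected tests need rerunning. Compared with EM fill-in that models arm, p values will tend to be larger. Compared with EM fill-in that omits arm, the correction removes the dilution of the effect.

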## Methods

### Study Design

A 2-arm, parallel, open-label RCT design was used to investigate the impact of a personalized mHealth intervention versus standard care on primary and secondary health outcomes. Eligible participants were randomized to either the intervention or the standard care control condition using a computerized random number generator. Assessments took place before randomization (T0; baseline), at 12 weeks (T1; intervention end), and at 24 weeks (T2; follow-up). The study was not blinded.

On completion of the study, a series of semistructured interviews were carried out to assess retrospective acceptability of the intervention from the perspective of the recipients. Purposeful maximum variation sampling was used. The theoretical framework of acceptability of health care interventions was used as a topic guide [22]. Specifically, open-ended questions were asked regarding participant’s affective attitude toward the intervention, the intervention’s coherence, participant burden, perceived effectiveness, and participants’ sense of self-efficacy.

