#### Recruitment and Consent

The clinical team identified 159 eligible participants who were identified sequentially from the oncology outpatient waiting list. The research team contacted them by telephone and described the aims and design of the study. Prospective participants who were interested in the study were sent an invitation letter, participant information sheet, and consent form. Informed written consent was provided by 123 participants (77.3% response rate) who attended baseline assessments. Participant characteristics are described in Table 4.

Of the 36 participants who did not consent to participate, 28 were not interested, 3 were waiting for surgery, 1 had chronic obstructive pulmonary disease, 1 was undergoing recurrence workup, 2 had young children, and 1 did not drive (see Figure 2).

**Table 4 table4:** Participants’ characteristics at baseline assessment.

Characteristics		Control	Intervention	2-tailed *t* test (*df*)	*P* value
Age, mean (SD)		59.24 (7.65)	55.61 (8.05)	2.39 (105)	.02
Weight (kg), mean (SD)		87.10 (16.32)	84.18 (13.98)	0.99 (105)	.32
BMI^a^ (kg/m^2^), mean (SD)		32.64 (5.41)	30.33 (3.99)	2.53 (105)	.01
Gender, female:male		49:4	42:12	—^b^	—

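### The pre-randomisation value is analysed as a third response level, not a covariate, which at the plan's own correlation of 0.3 costs about 35% of the information in a single-visit contrast

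*Protocol article*

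**What the plan says.** Study Design fixes the timing of the measurements: "Assessments took place before randomization (T0; baseline), at 12 weeks (T1; intervention end), and at 24 weeks (T2; follow-up". T0 therefore cannot be affected by the intervention.

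Statistical Analysis nevertheless makes T0 one of the three levels of the outcome: "A series of 3 (baseline, T1, and T2) × 2 (control and intervention) mixed ANOVAs will be performed to determine the efficacy". This covers the clinical, psychological and health behaviour measures. No covariate is named, and the section does not say whether efficacy is read from the arm-by-time interaction or from the group main effect. Average daily step count has its own *t*-tests and is outside this point.

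Sample Size uses the same structure: "With 2 groups (intervention and control), 3 measurements (baseline, time 1, and time 2", with "an assumed correlation among repeated measures of 0.3", "a small-medium effect size and a power of 0.8", and the result that "the recommended sample size for repeated measures analysis of variance (ANOVA) was 102".

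Table 4 (under Recruitment and Consent) gives baseline BMI as 32.64 (SD 5.41) in control and 30.33 (SD 3.99) in intervention, *P* = .01. Its degrees of freedom (105) and its sex counts (49 + 4 = 53 and 42 + 12 = 54) show that it describes 107 people, not the 123 randomised.

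**The concern.** A value taken before allocation tells us about the patient, not about the treatment. Used as a covariate, it removes noise from the arm comparison. Used as a response level, it enters each contrast with a fixed coefficient of −1, whatever its correlation with the later values. When that correlation is low, subtracting it adds more noise than it removes. The plan assumes a low correlation, 0.3, for all outcomes, and its many questionnaire outcomes are where such a value could apply. At stake is power that could be had from data already collected.

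There is a second, conditional issue. The arms differ at baseline on BMI. An analysis that does not adjust for baseline leaves that gap in the results, with a different sign in the two between-arm effects that the ANOVA prints.

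**Working it through.** **Inputs.** From the protocol article: 2 groups, 3 measurements, correlation r = 0.3, power 0.8, N = 102 (51 per arm), baseline BMI 32.64 and 30.33. Assumed, because the document does not give them: alpha 0.05, a numerical value for the small-medium effect, equal variances and equal correlations across visits, a 0.5 SD effect for the power illustration, and r = 0.9 to 0.95 as a possible range for BMI.

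**The plan's own figure.** For the arm-by-time interaction, λ = N f² m / (1 − r). With f = 0.15, λ = 102 × 0.0225 × 3 / 0.7 = 9.84 on 2 and 200 degrees of freedom, giving power 0.80. So 102 is reproduced. The within-subject time test has the same formula and gives the same N. The group main effect would need f of about 0.205.

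**Variance per arm, in units of SD².**

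| Contrast | Formula | r = 0.3 |
|---|---|---|
| T1 − T0 (change) | 2(1 − r) | 1.40 |
| T1 alone, T0 ignored | 1 | 1.00 |
| T1 adjusted for T0 | 1 − r² | 0.91 |
| Mean of T1 and T2, minus T0 | 1.5(1 − r) | 1.05 |
| Mean of T1 and T2, adjusted for T0 | (1 + r)/2 − r² | 0.56 |

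Single visit: 0.91 / 1.40 = 0.65, a loss of 35%. Average of both visits: 0.56 / 1.05 = 0.53, a loss of 47%. For the planned 2-df interaction, the loss relative to a baseline-adjusted analysis depends on the effect pattern: 47% if the effect is equal at both visits, 40% if it halves at one, 18% if it is present at one visit only.

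**Dependence on r.** The single-visit ratio is (1 + r)/2. The loss is 35% at 0.3, 25% at 0.5, 15% at 0.7, 5% at 0.9 and 2.5% at 0.95.

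**Power, 51 per arm, 0.5 SD effect, r = 0.3.** SE = √(2 × variance / 51).

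- T1 change: SE 0.234, ratio 2.13, power 56% by noncentral *t*, 57% by simulation.
- T1 adjusted: SE 0.189, ratio 2.65, power 75%.
- Averaged change: SE 0.203, ratio 2.46, power 68% by noncentral *t*, 67% by simulation.
- Averaged, adjusted: SE 0.148, ratio 3.37, power 92%.

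**BMI, given the observed gap and no true effect.** Gap = 32.64 − 30.33 = 2.31 kg/m². The expected later gap is r × 2.31, so the change contrast shifts by (1 − r) × 2.31 against the intervention. The group main effect averages the three levels and shifts by (1 + 2r)/3 × 2.31 in its favour.

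| r | Change contrast, against intervention | Group main effect, in favour |
|---|---|---|
| 0.3 | 1.62 | 1.23 |
| 0.9 (assumed) | 0.23 | 2.16 |
| 0.95 (assumed) | 0.12 | 2.23 |

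In simulation with 53 and 54 people and the gap held fixed, the three-level interaction rejects in about 27% of runs at r = 0.3, about 7.6% at 0.9 and 6.4% at 0.95. The baseline-adjusted test stays near 5%. Without conditioning on the gap, the interaction rejects near its nominal 5% (5.6% simulated).

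**The case against.** The strongest reply is that the planned interaction test is valid. It holds its error rate over repeated randomisations and is unbiased in that sense, so a reader who infers that the ANOVA is simply biased goes too far. That stands: the distortion exists only conditional on the observed imbalance, and for the interaction it works against an efficacy claim.

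A reader might also infer a near-certain false positive on BMI. Simulated with the gap fixed, the group main effect rejects in 94% of runs at r = 0.9 and 98% at 0.95. But no section names that effect as the efficacy test. The Procedure section speaks of improvement by 12 weeks and its maintenance, which is arm-by-time, and 102 reproduces at f = 0.15 for the interaction. What remains is that Statistical Analysis does not say which effect is read.

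The two harms also do not peak together. The 35% loss needs r = 0.3. If BMI tracks at 0.9 or above, its precision loss is 5% or less. The document gives no correlation by outcome, so 0.9 to 0.95 is an assumption. This stands and limits the point for BMI and weight.

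Setting the interaction's power of about 58% against 91% for the adjusted average would exaggerate the gain, because it compares a 2-df test with a 1-df one. Like for like, the average gains from about 67% to 92%.

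Nor can the BMI gap be called pure chance. Table 4 omits 16 of the 123 randomised, so post-randomisation non-attendance may contribute, and adjustment is not a guaranteed cure for that.

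Finally, covariates are often left to an analysis plan that is not shown here. That does not answer the point, because the article fixes T0 as a response level. Adding it as a covariate would replace the stated model.

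**Conclusion.** The concern holds as a matter of efficiency, with a conditional caution on BMI. At the plan's own r = 0.3, treating T0 as a response costs 35% of the information in a single-visit contrast: T1 power of about 57% instead of 75%, for an assumed 0.5 SD effect and 51 per arm. The cost shrinks as correlation rises and is small for any outcome that tracks strongly. Given the published BMI gap, the change contrast is shifted against the intervention by 1.6 kg/m² at r = 0.3, or 0.23 to 0.12 at an assumed 0.9 to 0.95. The group main effect would carry most of the gap the other way. The plan is not invalid, but it gives up precision and leaves open which effect counts. The sizes rest on equal variances and correlations across visits.

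**What to change.** For every outcome with a T0 value, replace the 3 × 2 ANOVA by a model with T1 and T2 only as responses (a linear mixed model, or ANCOVA per visit). Include that outcome's own T0 value as covariate, with arm and, in the mixed model, visit and arm-by-visit. State that efficacy is read from the adjusted arm differences and not from an ANOVA group main effect.

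Any adjustment for age, sex or baseline BMI (for other outcomes) would be chosen after Table 4 had been seen. It belongs in a sensitivity analysis labelled as such.

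No new data are needed, since all 123 attended the baseline assessment. The cost is a change of model while, according to the Results section, analysis is under way. Disclose the change with its date and reason, and report the planned ANOVA interaction beside the adjusted results.
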